incidence of the malaria disease (uncomplicated and severe malaria). A cross-sectional survey will be carried after the third round in November/December to determine the coverage of SMC, the prevalence of the malaria parasitemia and anemia as well as humoral and cellular immune responses in a randomly selected number of children. Data collected in year 1 will be analyzed to determine the optimal delivery method (DDD+ DOT or DDD+NDOT or FPD+ DOT or FPD + NDOT) based primarily on the coverage of SMC and secondarily on the incidence of clinical malaria. The difference in SMC coverage is expected to be reflected in the incidence of clinical malaria, and the latter will be used to support the data on coverage of SMC. [Should there be no statistically significant difference between the arms in coverage and incidence of the disease, the easiest method of the delivery will be recommended for Year 2.](#)

In Year 2, SMC will be implemented using the optimal delivery system (determined in Year 1) in two sub-districts assigned during Year 2 after a census of children under 5 years of age. Villages in these two newly selected sub-districts will be randomized to receive either three or four SMC rounds during the transmission season starting in August. Baseline data on malaria parasitemia, markers of resistance to SP and AQ and immune responses to malaria antigens will be collected at baseline prior to the intervention in these two sub districts through a cross-sectional survey. In order to assess the effect of the fourth dose of SP and AQ, children will be followed passively to measure incidence rate of clinical malaria, and a cross-sectional survey will be carried out at the end of the malaria transmission season in November/December in a randomly selected sample of children to determine the prevalence of malaria infection, anemia, and humoral and cellular immune responses. Children that participated in Year 1 will continue to receive three rounds of SMC in Year 2 using the best delivery method identified in Year 1. The choice of the optimal number of doses will be based on the incidence of clinical malaria between the two arms of children in the two newly selected districts. An absolute difference of 7.5 episodes per 100 children per year will be considered meaningful.

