## 5. Statistical Considerations and Data Analysis

### A. Sample Size and Power Calculation(s)

*Cross-sectional surveys.* Sample size for cross-sectional surveys will be based on the SMC coverage. Assuming 60% average coverage of SMC by the combination of nonoptimal methods (pools of two groups), 300 children/arm will be needed to detect 10% increase in average coverage for two pooled groups with at least 85% power correcting for multiple tests and using two Fisher's exact tests. To account for cluster sampling with a minimum 10 clusters per arm, interclass correlation of 0.01 (based on a previous trial showing vaccine coverage (Dicko et al BMC Pub Health 2011), and 5% missing data, 446 children will be surveyed per group (total of 1784 children).

*Passive surveillance.*

Assuming a clinical malaria attack rate of 0.3 per child per year in “3 rounds” arm, to detect an absolute difference in attack rate of the 0.075 episode/chil/ year (corresponding to 25% reduction) in the “4 rounds” arm, with a one sided p-value of 0.025 and power of 80%, using a quasi poisson model accounting for 20 equally sized clusters per arm with intraclass correlation of 0.01 and 5% missing data we will need 1386 per arm, or 2,772 subjects total.

*Immunological parameters.* We will base our sample size calculations for immunological endpoints on the humoral immune response to AMA1. We select this response because AMA1 is highly immunogenic from among malaria antigens. Also, the intervention in this trial is directed at reducing the blood stage burden of parasites during the malaria season, and the response to AMA1 reflects exposure to blood stage forms of the parasite. In earlier serology studies of young children participating in an AMA-1 vaccine trial in Bancoumana, Mali (Sagara et al, Vaccine, 2009), we observed the peak antibody titer against AMA1 to occur near the end of the malaria season (among children receiving control vaccine), with geometric mean antibody levels of 120 antibody units (95% CI, 70-205). Antibody levels just prior to the start of the malaria season (before vaccination) were 40 (25-75) antibody units. Based on these data, 467 subjects per

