### **B. Planned Interim Analyses (if applicable)**

At the end of the first transmission season, data will be analyzed to determine the optimal mode of delivery by comparing primarily the coverage of SMC and secondarily the incidence rate of the clinical malaria between the four intervention arms. In addition, descriptive analysis of the baseline frequencies of the immunological parameters, and molecular markers of the resistance of *P. falciparum* to SP and AQ, will also be performed at the end of Year 1.

Data collected in Year 2 will be used to determine the optimal frequency of the SMC rounds by comparing primarily the incidence of clinical malaria and secondarily the parasite prevalence at the end of season between the 2 arms. Descriptive analysis of immunological parameters and markers of drug resistance will also be performed.

Details of the statistical methods are provided below in the final analysis plan.

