### **C. Final Analysis Plan**

*Describe statistical methods that will be used to analyze data.*

Data will be entered and verified using DataFax. The cleaned database will be exported to Stata (Houston Texas USA) or SAS for analysis. An intention-to-treat analysis will be used except for the immunological endpoints for which the exact number of the SMC treatments received will be considered.

SMC coverage will be determined using the information on the SMC card and from interview of parent or care giver and will be determined as the proportion of children who received all the treatments at all the SMC rounds during the transmission season. The proportion of children who received at least the first treatment dose of the SMC will be also estimated as secondary endpoints for SMC coverage. SMC coverage will be compared between arms and years of

interventions with 95% confidence intervals adjusted for cluster design (using cluster option in Stata for example). The DDD+NDOT arm will be considered as control group.

The census of the children will be updated at each round and at the end of the transmission season to allow a good estimation of person-time of follow-up. Cases of the clinical malaria will be recorded and the incidence rate of the clinical malaria defined as the number of clinical malaria episodes divided by total child days at risk. Children will not be considered at risk 21 days after a clinical malaria episode. Incidence rates of clinical malaria will be compared between treatment arms using generalized estimating equation to estimate the incidence rate ratio, with adjustment for age, previous SMC regimens and the lack of independence among repeated episodes in the same child.

Proportions of other secondary endpoints such as parasite prevalence, prevalence of anemia and frequency of molecular markers of resistance to SP and AQ and adverse events associated with study drugs will be estimated and compared between groups using generalized linear models with 95% confidence intervals, adjusted for cluster design and potential confounding variables such as age and use of ITN.

Differences at baseline will be compared using Chi-squared or Fisher's exact tests as appropriate for categorical variables and by analysis of the variances for quantitative variables that are normally distributed. Nonparametric tests will be used for non-normally distributed data.

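### The Year 1 coverage outcome is powered on two pooled factorial contrasts, but the analysis described is a four-arm comparison against DDD+NDOT, to which the stated power does not belong

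*Protocol*

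**What the plan says.** **Sizing.** Under Sample Size and Power Calculation(s), the cross-sectional survey is based on pooled halves of the 2x2 design: "Assuming 60% average coverage of SMC by the combination of nonoptimal methods (pools of two groups), 300 children/arm will be needed". The aim of the calculation is given as "to detect 10% increase in average coverage for two pooled groups with at least 85% power". Its error control and test are described separately as "correcting for multiple tests and using two Fisher's exact tests". The figure is then inflated for a "minimum 10 clusters per arm, interclass correlation of 0.01" and 5% missing data, to 446 per group and 1784 in total. The Rationale frames the question the same way, as DDD against FPD and DOT against NDOT, and villages are randomised on each factor.

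**Analysis.** Planned Interim Analyses compares coverage first and "secondarily the incidence rate of the clinical malaria between the four intervention arms", and refers to the Final Analysis Plan for methods. That section compares coverage between arms, with 95% confidence intervals adjusted for the cluster design, and states: "The DDD+NDOT arm will be considered as control group". It mentions neither a pooled contrast nor a correction for multiple comparisons.

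**Decision.** Under Overall design, one of the four combinations is chosen, primarily on coverage. If neither coverage nor incidence differs significantly between arms, "the easiest method of the delivery will be recommended for Year 2".

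The French text repeats both sides (sections 5.1, 5.2 and 5.3), so this is not a stray sentence in one language.

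**The concern.** Coverage is a primary outcome, and its result sets the delivery mode for Years 2 and 3. A single-cell control has no role in two marginal contrasts. It belongs to three comparisons of one arm with another, each on half as many children as the pooled contrasts use. The protocol therefore powers one analysis and describes another.

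Two things are at stake. Without a correction, the between-arm comparisons lose the error control that the sizing assumed. With a correction, they lose power. Because the absence of a significant difference feeds the rule to adopt the easiest method, lost power can carry through to the delivery mode chosen.

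**Working it through.** **Inputs** (Sample Size and Power Calculation(s)): coverage 60% versus 70% (the 10% increase read as absolute); 300 children per arm before inflation; 10 clusters per arm; intraclass correlation 0.01; 5% missing. Alpha is not given. I assume two-sided 0.05 overall, so 0.025 for each of the two pooled tests.

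**1. Reproduce the survey size.** With N analysed per arm in 10 clusters, N = 300 × [1 + (N/10 − 1) × 0.01]. So N = 300 × 0.99 / (1 − 0.3) = 424.3, a design effect of 424.3/300 = 1.414. Then 424.3/0.95 = 446.6, which matches the stated 446. The effective size is about 300 per arm and 600 per pooled side.

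**2. Power formula.** Power = Φ{[δ√n − z√(2p̄(1−p̄))] / √(p₁q₁ + p₂q₂)}, with δ = 0.10, √(2 × 0.65 × 0.35) = 0.6745 and √(0.24 + 0.21) = 0.6708.

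| Comparison | n per side | Two-sided alpha | z | Power | Exact Fisher |
|---|---|---|---|---|---|
| Pooled contrast | 600 | 0.025 | 2.241 | Φ(1.398) = 92% | 91% |
| One arm vs DDD+NDOT | 300 | 0.05 | 1.960 | Φ(0.611) = 73% | 70% |
| One arm vs DDD+NDOT | 300 | 0.05/3 | 2.394 | Φ(0.175) = 57% | 54% |

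The pooled contrast supports the stated figure of at least 85%. The single-arm comparison does not, with or without the correction.

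**3. False differences when all four arms are equal.** For the pooled pair, 1 − 0.975² = 4.9%. For three unadjusted comparisons sharing one control, simulation with 300 effective children per arm gives about 12.5%.

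**4. Chance that no coverage comparison is significant** (simulation, same effective sizes):

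| True pattern | vs control, unadjusted | vs control, Bonferroni | Two pooled contrasts |
|---|---|---|---|
| One factor adds 10 points (60/60/70/70) | 12% | 26% | 8% |
| Only one combination, not DDD+NDOT, is 10 points better (60/60/60/70) | 23% | 41% | 45% |

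In the first pattern, two of the three comparisons with DDD+NDOT carry the 10-point gap, so the plan has two chances to see it. In the second, each marginal difference shrinks to 5 points and each pooled contrast has only about 33% power.

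**5. What pairwise comparisons would need.** For 85% power, the effective size is 407 per arm at 0.05 or 534 at 0.05/3. Inflating as in step 1: 407 × 0.99/(1 − 0.407)/0.95 = 715, and 534 × 0.99/(1 − 0.534)/0.95 = 1194 surveyed per arm, against the planned 446.

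**The case against.** The best defence is that naming a reference arm does not rule out a factorial analysis. DDD+NDOT can simply be the cell with both factors at their reference level in a two-factor model, and the Rationale, the randomisation and the sizing all show that the marginal contrasts were intended. That is fair as to intent, and it is why the sentence need not be deleted. It does not remove the mismatch: the section to which the protocol refers for its methods describes only a comparison between arms.

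Three stronger readings are tempting, and the documents do not support them.

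- **That the stated analysis has 57% power.** That figure needs a three-comparison correction which the plan does not state. The sizing text's correction concerns its own two tests. Under the plan as written, a single comparison has 73% power, and the chance of finding some difference from control when one factor works is about 88% (100 − 12).
- **That a true 10-point gain is missed, and the easiest method adopted, 43% of the time rather than 8%.** The 43% is the miss rate of one corrected pairwise test (100 − 57). The fallback rule looks across the arms and also requires no significant difference in incidence. On coverage alone the figures are 12% or 26%, against 8%, and the incidence condition can only lower them.
- **That some pairs, such as FPD+NDOT and FPD+DOT, are never compared.** A comparison between arms does not exclude them.

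The pooled contrasts are also not better in every case. If only one combination is superior, they miss more often than the comparisons with control.

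**Conclusion.** The inconsistency is real and concerns a primary outcome, but its effect is moderate. The claim of at least 85% power holds for the two pooled contrasts (about 92% each). It does not hold for one arm against DDD+NDOT (about 73% unadjusted). Left unadjusted, the described comparisons raise the chance of a false difference from about 5% to about 12.5%. If one factor adds 10 points, the chance of seeing no significant coverage difference rises by about 4 percentage points unadjusted, or about 18 if a Bonferroni correction were applied.

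These figures assume overall two-sided alpha of 0.05, an absolute difference of 60% versus 70%, an intraclass correlation of 0.01 as stated, and normal approximations on effective sample sizes. Exact Fisher power is about 1 point lower for the pooled contrast and about 3 points lower for the pairwise comparisons. Allowing for only 10 clusters per arm in the reference distribution would lower the pairwise figures somewhat further. If both factors work additively, the chance of finding no difference is under 1% whichever analysis is used.

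**What to change.** In the Final Analysis Plan, and in section 5.3 of the French text, name the primary Year 1 coverage analysis as the two marginal contrasts, FPD versus DDD and DOT versus NDOT. Test each at two-sided 0.025, from one model that contains both factors and allows for clustering by village. State the overall alpha in the sample size section. Report the interaction with its confidence interval and the four cell estimates as supportive. DDD+NDOT may stay as the reference cell of that model but should not define the primary comparisons. Align the wording under Planned Interim Analyses.

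This changes text only and keeps the planned 446 per group. Its cost is the weakness shown above when a single combination is superior (about 45% miss, against 23% unadjusted or 41% with Bonferroni for comparisons with control). The interaction and the four cells must therefore be in view when the delivery mode is chosen. The alternative, keeping arm-against-control comparisons as primary, would need a stated multiplicity rule and a much larger survey.

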**B. Study Outcome measure(s)**

The primary outcomes are:

1. SMC coverage for the determination of the optimal mode of delivery during Year 1. SMC coverage will be defined as proportion of the children who have received the three treatments doses at each of the three rounds of SMC.
2. Incidence of the clinical malaria for the optimal frequency of SMC in Year 2. Clinical malaria will be defined as signs and symptoms suggestive of malaria with positive RDT and/or positive blood smear.

Secondary trial outcomes of the study include:

1. Parasite prevalence defined as the proportion of children with a positive malaria blood smear and parasite density measured in Years 1, 2 and 3.
2. Prevalence of moderate anemia defined as hemoglobin concentration < 8 g/dL measured by hemoglobin analyzer.
3. Cellular and humoral antimalarial immune responses to malaria parasites.
4. Levels of cytokines and other host responses measured in sera/plasma or in immune cells.

5. Frequency of mutations at codons 51, 59, and 108 of the dhfr gene, 437 and 540 of the dhps gene, codon 76 in the *P. falciparum* chloroquine transporter gene (pfcr), and codon 86 of the *P. falciparum* multidrug resistance gene one (pfmdr1)

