#### ***Census and randomization***

Once community consent to the trial is obtained, a household census will be conducted and all households within the study areas with children under 5 years of age will be identified. At the time of census, a preliminary screening of potentially eligible children will be undertaken. Eligible children will be identified and written informed consent will be obtained from their caretakers for their inclusion in the trial. Children entered into the trial will be assigned a unique ID number and their demographic data (date of birth and/or age, and gender) will be collected.

The census will be updated at each SMC round and potentially eligible participants (such as children who did not reach the age of three months during the previous round) will be identified and screened for eligibility and enter into the study. This updated census will collect information on migration and death of children enrolled into the study for precise estimation of person-time of follow-up.

The unit of randomization will be village and all eligible children in a village will be allocated to the same study arm (DDD+ DOT or DDD+NDOT or FPD+ DOT or FPD + NDOT) to avoid confusion in Year 1. Villages in the selected sub-districts will be randomized at 1:1 ratio to receive either a door –to-door delivery (DDD) or fixed point distribution (FPD) of SMC. They will also be randomized to receive SMC as directly observed therapy (DOT) or a non-directly observed therapy (NDOT). In Year 2, villages in the two newly randomly selected districts will be randomized into two groups to receive either three or four rounds of SMC.

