## 5.3 Plan d'analyse final :

Les données seront saisies et vérifiées à l'aide de DataFax. La base des données nettoyée sera exportée vers Stata (Houston Texas USA) ou SAS pour l'analyse. Une analyse par intention de traiter sera utilisée, sauf pour les effets immunologiques pour lesquelles le nombre exact des traitements de la CPS reçus seront considérés.

La couverture de la CPS sera déterminée en utilisant les informations sur la carte CPS et de l'interview du parent ou tuteur et sera considérée comme étant la proportion d'enfants ayant reçu tous les traitements à tous les passages de la CPS pendant la saison de transmission. La proportion d'enfants ayant reçu au moins la première dose de traitement de la CPS sera également estimée comme critère secondaire de couverture de CPS. La couverture de la CPS sera comparée entre les bras avec les intervalles de confiance à 95% ajustés à l'échantillonnage en grappe. Le bras DPP + TNDS sera considéré comme groupe de contrôle. Le recensement des enfants sera mis à jour à chaque passage et à la fin de la saison de transmission pour permettre une bonne estimation de personne - temps de suivi. Les cas de paludisme maladie seront enregistrés et le taux d'incidence des accès palustres sera défini comme le nombre d'épisodes d'accès palustres divisé par le nombre total des jours où l'enfant est à risque. Les enfants ne seront pas considérés comme étant à risque 21 jours après un épisode de d'accès palustre. Les taux d'incidence d'accès palustre seront comparés entre les bras de traitement en utilisant les modèles d'équation d'estimation généralisée pour estimer les ratios des taux d'incidence avec ajustement pour l'âge, les régimes précédents de la CPS et le manque d'indépendance entre les épisodes répétés chez le même enfant.

La proportion des autres critères secondaires de jugement tels que la prévalence l'infection palustre, la prévalence de l'anémie et la fréquence des marqueurs moléculaires de la résistance à SP et AQ et les effets indésirables associés aux médicaments de l'étude seront estimés et comparés entre les groupes à l'aide de modèles linéaires généralisés avec des intervalles de confiance à 95% , ajustés pour l'échantillonnage en grappes et les variables de confusion potentielles , tels que l'âge et l'utilisation des MII.

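### The stated incidence analysis allows for repeat episodes within a child but does not name village, the randomised unit, and so conflicts with the model used to size the Year 2 comparison

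*Protocol*

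**What the plan says.** **Randomisation.** Section 4, Census and randomization: "The unit of randomization will be village and all eligible children in a village will be allocated to the same study arm". For Year 2, "villages in the two newly randomly selected districts will be randomized into two groups to receive either three or four rounds of SMC".

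**Outcome.** Section 3.B lists as a primary outcome "Incidence of the clinical malaria for the optimal frequency of SMC in Year 2". In Year 1, incidence is secondary to coverage in choosing the delivery mode (Section 4, Overall design; Section 5.B).

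**Sample size.** Section 5.A, Passive surveillance: "Assuming a clinical malaria attack rate of 0.3 per child per year" in the three-round arm; a difference of 0.075, "corresponding to 25% reduction"; one-sided 0.025; 80% power; 5% missing data; "using a quasi poisson model accounting for 20 equally sized clusters per arm with intraclass correlation of 0.01". The result is 1386 per arm, 2772 in total.

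**Analysis.** Section 5.C compares incidence by generalized estimating equations, with "adjustment for age, previous SMC regimens and the lack of independence among repeated episodes in the same child". The French version (5.3) has the same content, ending in "le manque d'indépendance entre les épisodes répétés chez le même enfant". In the same section of both versions, the coverage intervals and the models for the other secondary proportions are stated to allow for the cluster design. The incidence sentence is not.

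**The concern.** Children in one village share transmission intensity, a health worker and access to care, so their malaria counts are correlated. When whole villages are allocated, that correlation is part of the error of the arm comparison. A GEE whose cluster is the child treats children of one village as independent. A robust variance at child level does not repair this, because it captures only the correlation within each child's own record.

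The matter goes beyond detail that a protocol may leave to a later plan. Section 5.C names the model and the one source of dependence it allows for, and Section 5.B sends the reader there for the methods. A programmer following it closely would cluster on child. At stake are the test and confidence interval for the Year 2 primary comparison, and the supporting incidence comparison in Year 1, where the fallback to the easiest delivery method depends on finding no significant difference in coverage and incidence.

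**Working it through.** **Inputs (Section 5.A):** rates 0.30 and 0.225; one-sided 0.025; power 80%; 20 villages per arm; ICC 0.01; 5% missing; 1386 per arm.

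**1. The plan's own figure.** The two-rate Poisson formula gives the size without clustering:

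n0 = (q_α + q_β)² × (0.30 + 0.225) / 0.075²

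- Normal quantiles: (1.960 + 0.842)² × 93.33 = 733 per arm.
- t quantiles on 40 − 2 = 38 df: 772 per arm.

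Multiply by the design effect 1 + (m − 1) × 0.01, solve for 20 villages per arm, and divide by 0.95:

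- Normal quantiles: 1205 to 1256 per arm, depending on whether m counts analysed or enrolled children and on the difference or log-ratio form.
- t(38), m as enrolled children: 1354 (difference) or 1370 (log ratio), within 3% of 1386.

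With 1386 enrolled, 1317 analysed and a t(38) critical value, power is 81% to 82%. Without village clustering the requirement would be about 733/0.95 = 772 (normal) or 772/0.95 = 813 (t). The stated 1386 therefore includes an allowance for village clustering.

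**2. Design effect that a child-level analysis leaves out.**

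- Analysed children per village: 1386 × 0.95 / 20 = 65.8.
- Design effect: 1 + 64.8 × 0.01 = 1.648.
- Standard error understated by √1.648 = 1.284.

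**3. Actual error of the nominal test.**

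- One-sided: 1 − Φ(1.96 / 1.284) = 0.063, against 0.025.
- Two-sided: 0.127, against 0.05.

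With all 69.3 enrolled children per village the design effect is 1.683 and the errors are 6.5% and 13.1%.

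**4. Sensitivity to the ICC (65.8 per village).** Values other than 0.01 are assumptions.

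| ICC | Design effect | One-sided error | Two-sided error |
|---|---|---|---|
| 0.002 | 1.130 | 3.3% | 6.5% |
| 0.005 | 1.324 | 4.4% | 8.9% |
| 0.01 (protocol) | 1.648 | 6.3% | 12.7% |
| 0.02 | 2.297 | 9.8% | 19.6% |

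**5. Simulation.** Null trials were generated with 20 villages per arm, 66 children each and gamma-distributed village effects at ICC 0.01, with 20,000 replicates per scenario. A child-level robust analysis rejected in 6.2% to 6.5% (one-sided) and 12.5% to 13.0% (two-sided), with or without extra variation between children. A t-test on the 40 village rates rejected in 4.9% to 5.1% (two-sided).

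These figures are for Year 2. The protocol gives no incidence sample size for the four-arm Year 1 comparison, so no corresponding figure is derived for it.

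**The case against.** **Village adjustment may have been intended.** Section 5.A names a cluster-accounting model for this very comparison, and Section 5.C does not exclude village. A GEE clustered on village would also cover repeat episodes in a child. The incidence sentence looks generic as well: it adjusts for earlier SMC regimens, which the newly entered Year 2 sub-districts would not have had under this design. This stands. A reader might infer that the trial's analysis ignores village and that its error rate is inflated as a matter of fact. The documents support less: two sections disagree, and the inflation follows only if Section 5.C is carried out as written.

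**Significance is not the only basis for choosing the number of rounds.** A reader might infer that a false-positive test would by itself settle for four rounds. Section 4 also treats an absolute gap of 7.5 attacks per 100 children a year as meaningful. If that were applied to the observed difference, chance would rarely reach it: the true standard error at rate 0.3 is √(2 × 0.3 × 1.648 / 1317) = 0.027, so 0.075 is about 2.7 standard errors, or about 0.3% in the favourable direction under the null. The wording is not a formal rule, so the test still matters, but the error rates above are not the probability of a wrong decision. In Year 1, incidence only supports coverage, which is analysed with allowance for clustering.

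**The size depends on the ICC.** The protocol gives a source for 0.01 only for coverage, not for incidence. At 0.002 the two-sided error is 6.5%, a modest excess. Much larger inflation can be produced with ICCs of 0.05 or so, but nothing in the protocol points to such values.

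None of this removes the mismatch. The contrast with the neighbouring endpoints in Section 5.C, repeated in French, leaves the written instruction at child level.

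**Conclusion.** The point holds as an inconsistency with a conditional consequence. Section 5.C and its French counterpart state the incidence GEE with dependence within child only, contrary to the unit of randomisation, to the model behind the 1386 per arm, and to the treatment of the other endpoints in the same section. Run that way, the Year 2 test would have a true error of about 6.3% one-sided against 2.5%, or 12.7% two-sided against 5%, and confidence intervals too narrow by a factor of 1.28. This rests on the protocol's ICC of 0.01, 20 equal villages per arm and 5% loss; between ICC 0.002 and 0.02 the two-sided error runs from about 6.5% to about 20%. What is affected is the significance test and the interval, not the whole basis for choosing the number of rounds. The sections should be reconciled before the Year 1 and Year 2 incidence analyses are run.

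**What to change.** Keep the existing sentence in Section 5.C with its covariates (age and previous SMC regimens), and add, for example: *The GEE will use village as the clustering unit, which also covers dependence between episodes in one child, with robust standard errors and a small-sample correction suited to the number of villages in each comparison.* Make the same addition in section 5.3 of the French version. The correction should be set separately for the two-arm Year 2 and four-arm Year 1 comparisons, because the number of villages and arms differs; its exact form can be left to the statistical analysis plan.

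Cost: one added sentence in each language. At ICC 0.01, confidence intervals become about 28% wider than under child-only clustering. The planned 1386 per arm already allows for this, with power of about 81% to 82% at a t(38) critical value, so no additional children or villages are needed.
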